**Fig. 3 Fig3:**
[figure not shown]
Study design diagram (**a** Pre-and post-evaluation study; **b** Controlled cohort study)

The cohort study will compare two study populations: the intervention group (IG) consisting of patients attending RASP, and the control group (CG), comprising a cohort of patients who were referred by PHP to the MHAP central intake services prior to RASP implementation (Fig. 3b). This design allows researchers to examine whether possible changes in high-cost health services utilization are associated with the intervention (RASP).

A cross-sectional evaluation of mental health outcomes at program entry will be employed to evaluate the prevalence and correlates of the various psychological conditions of the assisted population.

Patient experience and satisfaction will be assessed using both quantitative and qualitative data. The quantitative data will be extracted from the program's satisfaction survey, while the qualitative data will be gathered from a purposive sub-sample of the overall study population. The selected sub-sample will be invited to participate in focus group discussions as part of a sub-study to gain deeper insights into their experiences and perspectives. Key informant interviews will be conducted to obtain qualitative insights from various healthcare partners, including directors, psychiatrists, primary healthcare providers, MHA service leaders, and community organizations. These interviews will focus on their perceptions regarding the impact of RASP on patients' access to community mental health care and the support it provides for primary care providers. Qualitative descriptive methodology and thematic analysis will be employed to generate and refine the information and identify patterns or themes within the qualitative data [35, 36]. This research protocol has been approved by the Research Ethics Board at Nova Scotia Health (REB file #1028254). The Gantt chart timeline is presented in the supplementary material (Table S1).

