### Participants and data collection

All RASP patients receive a consent form as part of their intake process, allowing access to their health services utilization records. Only those who sign the consent form will be part of the study. While consent is obtained during the initial assessment for ongoing patient recruitment, data collection is scheduled to commence after the program's first year, in April 2024. Service utilization data will extracted from provincial information systems retrospectively and prospectively at 2-time points: one year pre- and one-year post-assessment date at RASP. In addition, sociodemographic and mental health assessment information, including results from patient-completed validated scales and psychiatry diagnosis, and patient satisfaction will be extracted from routine paper-based initial screening forms. Patient satisfaction quantitative data will be extracted from RASP's patient satisfaction survey, available in a paper-based format and completed immediately after the assessment or REDCap online survey link sent via text message to all patients attending the service just after the assessment appointment.

The control group for the cohort study will comprise patients referred to the MHAP Central Intake Services by a PHP before RASP implementation. The periods for inclusion in the control group will be May 2017 to May 2019 (pre-COVID) and May 2020 to May 2022 (during COVID). By examining the data from these two time points (pre-COVID and during COVID) and comparing them with each other and with data during the RASP implementation period, we will be able to evaluate the impact of the pandemic on health services utilization as well as the impact of RASP implementation in comparison with both the pre-pandemic and during the pandemic periods. Ethics approval for exemption from requiring informed consent for all control group patients has been granted by the Research Ethics Board at Nova Scotia Health (REB file #1028254), allowing control group patients' sociodemographic and health services utilization information from provincial administrative databases to be accessed by the investigators.

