### Sample size considerations

With two staff psychiatrists and a clinical coordinator, we expect an average of six patients to receive comprehensive psychiatric assessments at the RASP each working day. Thus, we anticipate that the total number of patients accessing the service over the 24-month data collection period would be at least 2500. We also expect the sample size for the control population (patients whom a primary care provider referred to the MHAP Central Intake Services between May 2020 and May 2022) to be at least equal to the numbers seen at the RASP over a similar two-year time frame. Therefore, the data set to be generated from an overall sample of 5000 patients in this study would be large. With the assumption that the implementation of RASP will lead to at least a 10% reduction in high-cost health services utilization one-year post initial referral from a primary care provider for patients attending the service compared to patients who were offered a future appointment to see a mental health clinician as an entry point to the community mental health program, a power of 90% (β = 0.1) and a two-sided significance level of α = 0.05, and assuming an aggregated mean high cost health services utilization of 10 (SD =1) for the control population, we estimated that a sample size of 525 per group would be sufficient. Given that we expect at least 2500 patients per group in our study, it is highly probable that our study has more than sufficient power to detect the projected differences in high-intensity/cost health services utilization between the two groups.

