### Data analysis

#### Quantitative analysis

Quantitative data will be analyzed using descriptive and inferential statistics by using SPSS version 26 for Windows [46]. First, we will summarize the study participants' sociodemographic and clinical descriptive characteristics. Primary outcomes comparing the pre-and post-enrollment health services utilization for patients accessing RASP will be analyzed using descriptive and inferential statistical analysis, including Chi-Square and independent sample t-tests. For the primary outcome involving control populations, pre- and post-enrollment health services utilization variables will initially be compared using an analysis of covariance (ANCOVA) with the intervention condition (attended RASP) as the independent variable, the relevant health services utilization data one year pre attendance of appointment with RASP psychiatrist or community mental clinician as the covariate, and the relevant high-cost health services utilization data one year post attendance of appointment with a RASP psychiatrist or attendance with mental health clinicians in the community mental health program as the dependent variable. In each case, checks would be conducted to ensure no violation of regression slopes and reliable measurement of the covariate. We will perform sensitivity analyses of covariance to explore the impact of the imputation of data loss at each time point on health services utilization. In addition, we will perform propensity score matching and regression analyses adjusting for the periods pre-, during and post COVID-19 pandemic in order to strengthen the comparability of the groups and enhance the validity of the study's findings.

We will also use an ANCOVA to compare high-cost health services utilization data for one-year pre- and post-RASP attendance for the subset of patients who attend RASP and either participate or do not participate in the Text4Support RCT. For this analysis, the intervention condition (participants in the Text4Support RCT) will be the independent variable, the relevant health services utilization data one-year pre-attendance of appointment with RASP psychiatrist will be the covariate, and the relevant high-cost health services utilization data one-year post attendance of appointment with a RASP psychiatrist will be the dependent variable.

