#### Health economic evaluation

We will conduct an economic evaluation through an effectiveness-implementation science lens. Specifically, we will conduct a cost-consequence analysis (CCA) from a Canadian single-payer perspective. The CCA will involve a disaggregated comparison of the costs and benefits (consequences) associated with RASP. The disaggregated analysis reports the intervention effects for the relevant primary and secondary outcomes in their natural units to aid value for money assessments. The study design, population, setting, and location are described elsewhere in this proposal.

We will compare outcomes (ED visits, crisis calls and inpatient days) and costs in the intervention group to the control group. Costing includes costs associated with the pre-implementation, implementation, and ongoing costs. These costs will include space and utilities, new hires specific to RASP, supplies, materials, and equipment, travel costs, volunteer time, and other in-kind donations. We will exclude all research-related costs. These cost data will come from the project documents. In addition, we will collect cost data on health resource use from the case costing centre in the Nova Scotia Health, supplemented with data from the literature if necessary.

Costing will also include costs saved from avoided ED visits, crisis response services and inpatient treatments. Cost analyses will use Nova Scotia Health 2023 costs to ensure relevance to decision-makers. We will estimate the intervention effect for the outcomes using appropriate treatment-effect econometric models with bootstrapping to quantify the uncertainty around the estimates. To enable cost comparisons, the cost of the current models of community-based mental health services, which involve waitlisting of all non-urgent patients (regardless of referral source and reason for referral) to see a mental health clinician as a gateway to receipt of community mental health services, including psychiatry, will be compared with the costs of alternative treatments offered expeditiously through RASP and primary care and community providers. We will compute the net cost savings associated with RASP. Our economic analysis will follow guidelines for economic evaluations, including using probabilistic sensitivity analysis to quantify the uncertainty around the implementation costs [48].

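### The between-group comparison is powered on the year after referral but analysed on the year after the attended appointment, so waiting time counts as baseline, more of it in the waitlisted controls

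*Protocol article*

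**What the plan says.** All places are in the protocol article, Methods.

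- **Sample size considerations** powers the contrast on "at least a 10% reduction in high-cost health services utilization one-year post initial referral from a primary care provider". The comparator is "patients who were offered a future appointment to see a mental health clinician as an entry point to the community mental health program", that is, people offered an appointment, whether or not they came.
- **Study design** describes the control group as "comprising a cohort of patients who were referred by PHP to the MHAP central intake services prior to RASP implementation". Participants and data collection likewise defines controls by referral, and dates RASP utilization data as "one year pre- and one-year post-assessment date at RASP".
- **Quantitative analysis** sets the ANCOVA covariate as use "one year pre attendance of appointment with RASP psychiatrist or community mental clinician as the covariate", and the outcome as use "one year post attendance of appointment with a RASP psychiatrist or attendance with mental health clinicians in the community mental health program as the dependent". Both windows meet at the attended appointment.
- **Health economic evaluation** describes the existing model of care as one "which involve waitlisting of all non-urgent patients (regardless of referral source and reason for referral) to see a mental health clinician as a gateway". No section gives the length of that wait.
- **Hypothesis** expects waits for a psychiatrist to fall below 30 calendar days.
- **Study objectives**, research questions A, already needs the date on which Central Intake received the referral, to measure wait times.

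**The concern.** Shortening the interval between referral and first specialist contact is a stated aim of RASP. An index date at attendance places that interval before time zero in both groups, and the interval is expected to be longer in controls. Three things follow from the wording alone.

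1. Emergency visits, crisis visits and admissions during the wait are never counted as outcomes. If earlier access prevents some of them, the utilization contrast cannot show it.
2. The covariate is not a clean pre-referral baseline. It includes events that the care pathway itself may have influenced, over a longer stretch in one group than in the other.
3. Referred controls who never attended have no index date and leave the analysis, although the design and sample size sections define the group by referral or offer.

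The estimated quantity is then not the one the sample size section describes. The economic evaluation states no clock of its own. If it borrows these windows, it omits the cost of crises during the wait.

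**Working it through.** **The two definitions side by side**

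| | Sample size considerations | Quantitative analysis |
|---|---|---|
| Time zero | initial referral by the primary care provider | attended appointment |
| Control population | referred and offered an appointment | attended an appointment |
| Events during the wait | outcome | covariate |

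**The plan's own figure.** The 525 per group uses a control mean of 10, SD 1, a 10% reduction, two-sided 0.05 and 90% power. None of these inputs depends on the clock, so moving time zero leaves n unchanged for a given difference and SD. (Those inputs give 2 × (1.960 + 1.282)² × 1²/1² = 21.0, so 22 per group. That mismatch is a separate matter and has no bearing here.)

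**How much of the first post-referral year is lost.** Share = wait / 365. The control waits are assumptions.

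- RASP at its target ceiling: 30/365 = 8%
- Control 60 days: 60/365 = 16%
- Control 90 days: 90/365 = 25%
- Control 180 days: 180/365 = 49%
- Control 270 days: 270/365 = 74%

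**Illustration 1: use is raised only while waiting.** Assume 10 events a year before referral and after the appointment in both groups, *r* times that rate while waiting, a RASP wait of 30 days and a control wait of *W* days.

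- First-year use from referral: 10 × [1 + (r − 1) × wait/365].
- With r = 1.5 and W = 180: control 10 × (1 + 0.5 × 0.493) = 12.47; RASP 10 × (1 + 0.5 × 0.082) = 10.41. Reduction = 1 − 10.41/12.47 = 16.5%.
- Over r = 1.25 to 2 and W = 60 to 270 days, the referral-based reduction runs from 2.0% to 37.8%.
- The outcome year from attendance is 10 against 10, a 0% reduction in every case.
- The pre-attendance year in the r = 1.5, W = 180 case is 12.47 against 10.41, so the control covariate is 2.05 events higher. With an assumed ANCOVA slope of 0.3 to 0.7, adjustment moves the estimate against RASP by 0.3 × 2.05 = 0.62 to 0.7 × 2.05 = 1.44 events.

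**Illustration 2: use is raised for a fixed period after referral, and RASP has no effect.** Assume rate 1 a year, doubled for *D* days after referral in both groups, with a RASP wait of 20 days. Post-attendance mean = 1 + max(D − wait, 0)/365.

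| D (days) | Control wait (days) | RASP mean | Control mean | Apparent RASP excess |
|---|---|---|---|---|
| 30 | 90 | 1.027 | 1.000 | 2.7% |
| 90 | 45 | 1.192 | 1.123 | 6.1% |
| 90 | 60 | 1.192 | 1.082 | 10.1% |
| 90 | 90 | 1.192 | 1.000 | 19% |
| 180 | 180 | 1.438 | 1.000 | 43.8% |

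Both models work against RASP, but the amount depends on inputs that the article does not contain. These are raw post-year means, not ANCOVA estimates.

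**Calendar overlap with a referral anchor.** Assume uniform accrual from 1 May 2020 to 31 May 2022 (761 days) and launch on 1 April 2023. Controls referred from 1 April 2022 onward (61 days) have some follow-up after launch: 61/761 = 8%. If intake closes at the start of May 2022, the share is 30/730 = 4%.

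**The case against.** The strongest reply is that the referral wording is a single phrase in the sample size section. Elsewhere the article dates RASP utilization from the assessment, and the ANCOVA extends that logic to the control's appointment. Counting from first contact is a recognised choice: it estimates the effect of the service received, where a referral clock estimates the effect of the pathway. This stands to the extent that attendance is not invalid in itself. It does not remove the contradiction between the two sections, nor the fact that controls are recruited by referral.

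A second reply is that faster access is not lost, because days to a psychiatrist are a separate primary outcome and a research question asks about utilization before and after implementation without mention of attendance. The wait-time outcome shows that access was faster, but not whether crises were avoided as a result. The analysis section gives the before-and-after question no separate method. Propensity matching and adjustment for COVID period leave the index date where it is.

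A reader might infer more than the documents support:

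- **That RASP's effect as a whole is hidden.** It is not. Anything that happens after attendance is still counted.
- **That a useless programme would show about 19% more use than controls.** That figure needs a 90-day control wait, a 20-day RASP wait and a raised-use period exactly equal to the control wait. Other values give about 3% or over 40%.
- **That a fifth of during-COVID controls are contaminated by the RASP launch.** With an assumed 90-day wait, about 20% have at least one day of follow-up after launch, but only about 4.1% of their follow-up time lies there.
- **That every referred control should simply be kept.** RASP patients enter only by attending and signing consent. Requiring attendance in one group only would create a selection and immortal-time bias, probably in favour of RASP.

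**Conclusion.** The contradiction is explicit: the powered comparison starts at referral and the analysed comparison starts at attendance. As written, the ANCOVA moves a longer post-referral interval into the control baseline than into the RASP baseline. The utilization contrast then misses any benefit that comes from shorter waiting, and it adjusts for post-referral events. The unequal shift rests on the waitlisting described for controls and on RASP meeting its target of under 30 days.

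The size cannot be fixed from the article. Assumed control waits of 60 to 270 days take 16% to 74% of the first post-referral year out of the control outcome, against at most about 8% for RASP. What that does to the estimate depends also on use during the wait, and ranges from trivial to several times the hypothesised 10%. The choice should be settled before utilization data are extracted, because it determines what the between-group estimate means.

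**What to change.** - **Reconcile the two sections on one time zero.** Use the date Central Intake received the referral in both groups. The covariate is use in the 365 days before that date and the outcome is use in the 365 days after.
- **Apply the same attendance rule to both groups.** Either compare attenders with attenders, or compare all referred with all referred. The second is sound only if RASP referrals who did not attend or consent can also be included. The first still conditions on reaching an appointment, over a longer interval in controls, and the report should say so.
- **Limit this contrast to patients referred by a primary healthcare provider.** Walk-ins, planned for full implementation, have no described Central Intake referral date.
- **Report the attendance-anchored ANCOVA as a sensitivity analysis.** The gap between the two results shows how much the waiting interval matters.
- **Censor or exclude control follow-up after the April 2023 launch.** If censored, allow for the shorter observation time.

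The cost is revised wording and a re-dated extraction from the same systems, using a date already needed for wait times. Some late controls are affected: about 8% of the during-COVID cohort under uniform accrual, each losing about 30 days on average if censored (61/2 ≈ 30). The sample size does not change.

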For the qualitative component of the study, expected to take place after a year of RASP implementation, in April 2024, a sub-sample from the overall pool of the intervention population (RASP patients) will be invited by a research team member to participate in a focus group session. The inclusion criteria to participate in the qualitative sub-study are to provide consent and be available to attend a 1-hour focus group session, which will be audio-recorded. The focus group script will be developed by investigators, reviewed by healthcare partners, piloted with patients and adjusted as needed, before being used in the focus groups. A trained research team member will conduct the encounters, which may happen in person or via Zoom. The sample size for the qualitative component of the study cannot be predetermined because data saturation needs to be reached. Data analysis ends when no new themes and subthemes emerge across all analysts. However, based on what the literature suggests [37], we anticipate that 25-30 participants may be sufficient for this mixed-methods study. Participants will receive compensation for their time spent participating in the qualitative sub-study activities.

Healthcare partners involved with RASP will be also actively engaged in the qualitative evaluation of the program. Trained members of the research team will conduct individual key informant interviews, either virtually or in person, with program directors, psychiatrists, primary healthcare providers, MHA service leaders, and representatives from community organizations. These interviews aim to gather in-depth information about healthcare partners' experiences and opinions regarding the program, allowing for a comprehensive understanding of their perspectives.

Finally, a sub-population of RASP patients who opted to participate in the Text4Support RCT will also have their one-year pre- and post-RASP attendance health services utilization data collected and compared to patients who chose not to participate in the optional Text4Support RCT. RASP was launched in April 2023, with data collection ongoing. Table S2 demonstrates in detail the variables, sources and data collection time points.

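### A pre/during/post-COVID period term coded per patient coincides with RASP attendance, so the planned period adjustment cannot make RASP and control patients more comparable

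*Protocol article*

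**What the plan says.** All references are to the Methods of the protocol article.

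- **Control windows** (Participants and data collection): "The periods for inclusion in the control group will be May 2017 to May 2019 (pre-COVID) and May 2020 to May 2022 (during COVID"). All controls predate the program: "The control group for the cohort study will comprise patients referred to the MHAP Central Intake Services by a PHP before RASP implementation".
- **RASP start** (same section): "RASP was launched in April 2023, with data collection ongoing".
- **Three eras** (same section): the plan will compare the two control periods with each other and will assess "the impact of RASP implementation in comparison with both the pre-pandemic and during the pandemic periods".
- **Lead between-subject analysis** (Quantitative analysis): an ANCOVA with RASP attendance as the independent variable, utilization in the year before the appointment as covariate and utilization in the year after it as outcome. It has no period term.
- **Additional analysis** (same section): "we will perform propensity score matching and regression analyses adjusting for the periods pre-, during and post COVID-19 pandemic". The stated purpose is "in order to strengthen the comparability of the groups and enhance the validity of the study's findings".
- **Sample size** (Sample size considerations): the control population is described as patients "referred to the MHAP Central Intake Services between May 2020 and May 2022", which is one of the two control windows.

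**The concern.** Adjusting for a covariate helps only where treated and untreated patients share some of its values. On the stated dates, no RASP patient has an index date in a control window and no control has one in the RASP era. A period label attached to each patient therefore says nothing beyond group membership.

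The RASP-versus-control contrast is a primary outcome comparison and also feeds the economic evaluation, and the period step is presented as the means of making it credible. Statistical software would not necessarily stop. It may drop one of the two identical terms and print a coefficient for the other. A reader who saw that coefficient labelled as adjusted for pandemic period would believe that a bias had been removed when it had not been touched.

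**Working it through.** The plan gives no figure for this analysis. Its one computed sample size, 525 per group, does not enter the argument.

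**1. Code period per patient from the stated windows.**

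| Cohort | Index dates | Intercept | RASP | During | Post |
|---|---|---|---|---|---|
| Control, pre-COVID | May 2017–May 2019 | 1 | 0 | 0 | 0 |
| Control, during COVID | May 2020–May 2022 | 1 | 0 | 1 | 0 |
| RASP | from April 2023 | 1 | 1 | 0 | 1 |

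The RASP and post columns are identical. Three distinct rows cannot identify four parameters: 4 columns, rank 3. With prior-year utilization added and 2,500 patients per cohort (the plan gives at least 2,500 per group), there are 5 columns and rank 4. With only the during-COVID controls, the columns intercept, RASP, post and prior-year utilization number 4, with rank 3.

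**2. What this does to the estimate.** Write r for the RASP coefficient and p for the post coefficient. The data determine only r + p. The pairs (r, p) = (−1, 0), (0, −1) and (+1, −2) all give r + p = −1 and fit identically. They mean, in turn, that RASP lowers use, does nothing, and raises use.

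**3. Propensity score, if period is in it.** P(RASP | pre) = 0, P(RASP | during) = 0, P(RASP | post) = 1. Separation is complete and no RASP patient has a control to match.

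**4. What is left in the ANCOVA, which has no period term.** Suppose utilization in the RASP era differs by s from the control era for reasons unrelated to RASP, in both the prior year and the following year. With within-group slope b on the prior year, the ANCOVA group effect is biased by

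s − b·s = s(1 − b).

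The sample-size section assumes a control mean of 10 and a 10% effect, which is 1 unit. A 10% secular shift is s = 1. For assumed slopes:

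| b (assumed) | Bias = 1 × (1 − b) | Share of the hypothesised effect |
|---|---|---|
| 0.3 | 0.7 | 70% |
| 0.5 | 0.5 | 50% |
| 0.7 | 0.3 | 30% |

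A simulation with these pre/post correlations gave the same shares. Only a shift that arises wholly after the prior year passes through in full.

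**5. Would coding by calendar time of follow-up create overlap?** Count months from May 2020, so that April 2023 is month 35. Assume uniform inclusion over 24 months and a wait of w months before the appointment. The share of during-COVID control follow-up that falls after April 2023 is then (1 + w)²/576 for w up to 11:

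- w = 0: 1/576 = 0.2%
- w = 3: 16/576 = 3%
- w = 6: 49/576 = 9%
- w = 12: 29%, computed numerically because some follow-up years then lie wholly after April 2023

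The waits are assumptions. The overlap is slight unless waits are long.

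**The case against.** The strongest reply is that the coding in step 1 is not written down. The article gives no calendar bounds for the post period, does not say that period is a per-patient label, and does not list the propensity variables; the phrase about periods may modify only the regression. Other codings can be estimated. If the RASP era is merged with the during-COVID period, the model has full rank (4 of 4 columns). A model with two rows per patient (year before, year after), with shares of time in each period, also has full rank (6 of 6), because most of the RASP patients' own pre-years would be post-pandemic but unexposed.

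Part of this stands: the aliasing depends on the coding, and failure of the matching is conditional on period being in the score. But merging eras is not the three-period adjustment that is stated, and it assumes away the shift in question. The two-row model is not in the plan, whose between-group analysis uses one-year totals per patient, and it draws its identification mainly from the within-subject contrast under additive period effects.

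A reader might also infer more than the document supports:

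- *That RASP and controls cannot be compared at all.* The lead ANCOVA has no period term and remains estimable, and the aliasing does not touch the within-subject comparison.
- *That any secular change goes one for one into the RASP effect, so that a 10% drift equals the whole hypothesised 10%.* Step 4 shows that a shift present in both years is partly absorbed by the prior-year covariate.
- *That an interrupted time series or a concurrent comparator is required and comes from data in hand.* A monthly series needs data for May 2019 to May 2020 and May 2022 to April 2023, which lie outside the control windows. Concurrent referrals not booked to RASP would be selected by triage.

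Finally, separate comparisons with each control period are already foreseen in Participants and data collection, so that part of the remedy is largely the plan's own.

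**Conclusion.** The point holds for the period-adjusted analysis. With period coded per patient by cohort, overlap between RASP and controls on period is nil, the model is one rank short, and the adjusted RASP effect is not estimable. The step cannot deliver the comparability it is meant to provide. Enlarging the sample does not help.

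The RASP-versus-control contrast that can be computed remains confounded with calendar time. For a 10% shift present in both years and slopes of 0.3 to 0.7, about 70% to 30% of the hypothesised effect could be drift. The size of the shift and the slopes are illustrations, not figures from the plan.

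The conclusion rests on two readings: that RASP patients form the post level, which follows from the control labels, the April 2023 start and the three-way contrast; and that period is a per-patient label, which fits the one-year totals. The sample-size statement's use of only one control window is not part of the aliasing, but it leaves open which contrast the power claim covers.

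**What to change.** In the Quantitative analysis section:

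1. Remove period as a covariate and as a propensity variable from every RASP-versus-control model.
2. Match and adjust on patient characteristics and prior-year utilization.
3. Report RASP versus pre-COVID controls and RASP versus during-COVID controls as two separate contrasts.
4. State which contrast the sample-size statement refers to; as written it describes only the May 2020 to May 2022 cohort.
5. Do not describe either result as adjusted for the pandemic period, and list residual calendar-time confounding as a limitation.

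Period can still be used to compare the two control cohorts with each other.

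This costs a few sentences and no new data. What is lost is the COVID-adjusted claim, which the design could not support. An interrupted time series of Central Intake referrals, with a step at April 2023, is an optional extra that would address calendar time more directly. It needs data from outside the stated control windows, so it should be weighed separately.
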